## Abstract

**Introduction:** Frailty is very frequent among patients with chronic kidney disease (CKD) who are awaiting deceased donor kidney transplantation (KT), and transplant outcomes are worsened in those frail recipients. Frailty and poor fitness powerfully predict mortality, kidney graft survival, and healthcare utilization after KT. Intervention is essential to improve survival and quality of life for frail CKD patients, regardless of their age. Studies of post-transplant physical therapy intervention have been met with limited success, in large part due to high dropout rates. A pre-transplant clinical framework for multimodal prehabilitation interventions including physical therapy, nutritional measures, and psychological support scheduled during the KT waiting list period may improve patient retention and compliance, better mitigate the effects of frailty and poor fitness after KT, and improve main outcomes in frail CKD patients.

**Main Objective:** To study the effectiveness, feasibility, and safety of multimodal prehabilitation (exercise, nutritional plans, psychological advice) in KT candidates.

**Methods:** Randomized controlled clinical trial in 38 frail and 76 non-frail KT candidates. The prehabilitation program will consist of physical exercise (24 sessions, 8 weeks), nutritional supplementation, and psychological advice. The primary endpoint will be a composite achievement of clinical and functional main outcomes in frail and non-frail KT candidates at 90 days post-transplantation. Secondary outcomes include changes in exercise capacity, physical activity, gait speed, respiratory and peripheral muscle strength, muscle size, body composition, performance in activities of daily living (basic and instrumental), anxiety and depression symptoms, and health-related quality of life. Feasibility of the intervention will be also analyzed.

**Expected Results:** Multimodal prehabilitation is a feasible and effective intervention to decrease bad outcomes at 90 days post-KT by 25 and 12.5% in frail and non-frail patients, respectively.

**Clinical Trial Registration:**
clinicaltrials.gov (NCT04701398), date: 2021, January 8th (Protocol version: Frailmar_vers2).

## Introduction

### Background and rationale

Frailty is common among patients with chronic kidney disease (CKD), with a prevalence ranging from 7 to 42% among the non-dialysis population (1, 2) and reportedly around 73% in patients on haemodialysis (HD) (3, 4). Patients who are frail experience a decline in physical function and are at increased risk of adverse health outcomes, disability, and mortality (4–8). Candidates to kidney transplantation (KT) have a substantial burden of frailty, with a prevalence of around 20% (9, 10). Furthermore, frailty in KT candidates is associated with poor outcomes post-transplant (9, 11–14).

Efforts to improve outcomes in KT recipients have typically focused on post-transplant interventions. As candidates often have to wait months to years for a deceased donor or spend months identifying an appropriate live donor, pre-transplant intervention may be a uniquely fruitful avenue to explore (1). Moreover, pre- and post-KT physical activity is low among patients with end-stage renal disease (ESRD) (2). This inactivity is associated with poor graft and patient outcomes, including reduced cardio-respiratory fitness, impaired metabolic and nutritional status, reduced quality of life, and increased mortality (15, 16). While awaiting KT, candidates experience a profound loss of functional capacity due to the combination of aging, chronic conditions, and higher risk of frailty in addition to the stress of undergoing HD (17). By the time of KT, there is a high burden of patients with compromised physiology who cannot withstand the stressor of a major surgical intervention. Intervening through exercise training post-KT might not be optimal, given the steep decline in physical activity in the 1st year post-KT and poor compliance with prescribed rehabilitation therapy, as demonstrated through the high dropout rates in two published trials of post-KT exercise (18, 19).

In contrast, KT candidates might be more motivated to exercise knowing that they will be undergoing a major surgery in the coming months; in fact, patients and their providers strongly support prehabilitation in ESRD patients, particularly for vulnerable candidates such as those who are frail (20). Previous randomized controlled trials testing exercise interventions in patients with ESRD and KT recipients have been shown to improve graft function, quality of life, self-reported physical function, aerobic fitness, exercise capacity, and muscle strength, as well as reduced body fat and cardiovascular risk (16, 21–23).

Prehabilitation encompasses exercise-based therapies aimed to enhance preoperative functional capacity and improve tolerance for the upcoming stressor, resulting in better outcomes after the surgery (24). Prehabilitation increases physical activity and improves functional capacity before a major surgical stressor, contributing to a reduction of postoperative recovery time and a quicker return to functional ability (25–27). The prehabilitation interventions include exercise, nutrition, and anxiety-reduction elements. Programs to enhance recovery after surgery are aimed to improve patient outcomes and speed up recovery without compromising safety. In the only study published in KT recipients, enhanced recovery benefited both types of KT procedures (living and deceased grafts), improving patient satisfaction and reducing the length of the hospital stay (28).

Only one small study has assessed the possibility of prehabilitation for KT candidates (29); the intervention (18 participants) consisted of weekly physical therapy sessions at an outpatient center with at-home exercises. With 2 months of prehabilitation, participants improved their physical activity by 64% (*p* = 0.004) based on accelerometry data. Among five prehabilitation participants who received KT during the study, length of stay was shorter than for age-, sex-, and race-matched controls. There was a high level of satisfaction with the prehabilitation intervention, and participants overall reported that it was helping them prepare for KT. Participants noted an increase in physical function and energy, a sustained endurance, a means of weight control, and an improved attitude (29). Given the clinical relevance, it is mandatory to confirm these findings in a larger study with more KT recipients receiving prehabilitation.

Frailty is very frequent among CKD patients included in the waitlist for deceased donor KT, and post-transplant outcomes are worsened in those frail recipients. Moreover, frailty and poor fitness powerfully predict mortality, kidney graft survival, and healthcare utilization after KT. Thus, we hypothesize that a pre-transplant clinical framework for multimodal prehabilitation interventions including physical therapy, nutritional measures, and psychological support could improve patient retention and compliance, better mitigate the effects of frailty and poor fitness after KT, and improve main outcomes in frail CKD patients.

The main objective of this study is to assess effectiveness, feasibility, and safety of multimodal prehabilitation (exercise, nutritional plans, and psychological advice) in KT candidates in the context of a randomized controlled clinical trial. There are three specific objectives: (1) to study the potential effects of multimodal prehabilitation as a prognostic variable to predict the 90-day primary endpoint based on clinical and functional outcomes achieved in frail and non-frail KT candidates; (2) to assess the feasibility and safety of a multimodal prehabilitation program, with especial emphasis on the exercise component in KT candidates; and (3) to assess differences in exercise capacity, muscle function, functional status, and health-related quality of life in frail and non-frail candidates at 1-year post-KT follow-up.

## Methods and Analysis

### Trial Design

The FRAILMar Study is a controlled randomized clinical trial in candidates to KT assigned to the intervention group (multimodal prehabilitation) or control group (standard medical care), with an allocation ratio of 1:1, in a superiority framework. Results are stratified by frail and non-frail patient status. The study protocol is described following the Standard Protocol Items: Recommendations for Interventional Trials (SPIRIT) Statement (3).

### Study Settings

The Departments of Nephrology, Physical Medicine and Rehabilitation, Internal Medicine, Endocrinology, and Psychiatry of the Parc de Salut Mar Consortium (Hospital del Mar and Center Fòrum-Hospital del Mar), Barcelona, Spain will be involved in the trial. Members of the FRAILMAR Study Group are listed in the Appendix, by setting.

### Eligibility Criteria

Adult patients included in the waitlist for deceased donor KT from January 2020 to December 2022 will be eligible. Patients with known chronic muscle diseases and/or unable to perform the exercise plan will be excluded.

### Interventional Methods

The Multimodal Prehabilitation will be focused on behavioral change and the processes that trigger activity, combining physical exercise and motivation toward activity sessions to encourage the practice of moderate regular exercise and healthy habits. All patients in the intervention group, regardless of frailty status, will carry out the prehabilitation program of physical exercise, nutritional supplementation, and psychological advice.

#### Physical Exercise

The exercise component will consist of 1-hour sessions, three times per week for 8 weeks (total 24 sessions). Two of the weekly sessions will be supervised by a physical therapist and the third will be performed unsupervised at the patient's home. Patients will choose between on-site or home-based exercise with the physical therapist; in the case of exercising at home, patients will receive a training kit (cycle ergometer, weights, elastic bands, respiratory muscle trainer); the therapist will telematically supervise the sessions using an internet video call platform. Time schedules for conduction the intervention are detailed in Table 1.

**Table 1 T1:** Time schedules for conducting the intervention.

	**Mon**	**Tues**	**Wed**	**Thurs**	**Fri**	**Sat**
Mornings	Supervised		Supervised		Unsupervised	
Afternoons	Supervised		Supervised		Unsupervised	
Mornings		Supervised		Supervised		Unsupervised
Afternoons		Supervised		Supervised		Unsupervised

All patients will be given access to audiovisual material to support the unsupervised sessions. Each training session will consist of four elements: (1) warm-up (5 min); (2) continuous aerobic training performed on a cycle ergometer (20 min at 60% workload peak, increasing by 5 watts weekly if tolerated); (3) muscle strength exercises of upper and lower limbs (three sets of 10 repetitions of biceps curls, back and shoulder presses, hip flexion and knee extension, and self-weight squats; initial workload will be of 0.5 Kg and increase by 0.5 Kg weekly if tolerated); (4) inspiratory muscle training [five sets of 10 repetitions followed by 1–2 min of unloaded recovery breathing, once a day, 7 days a week for 8 weeks, using an inspiratory muscle trainer (Orygen Inspiratory One-way Valve, Forumed, Spain) at a rate of 15–20 breaths/min; training loads will be set at 30% of maximal inspiratory pressures (PImax) and adjusted weekly by 10 cmH_2_O if tolerated]; and (5) muscle stretching cool-down (5 min).

After completing the 8-week sessions, patients will be encouraged to continue exercising at home or community sports facilities, and will receive coaching from the physical therapist once a month till KT. All study participants shall be removed from the KT waitlist during this period, and re-included after the 12-week assessment, respecting their original placement on the waitlist.

#### Nutritional Supplementation

Well-nourished patients with normal weight or overweight will receive advice to stabilize diet or improve habits, respectively, and just after every exercise session lyophilized protein supplement (20 g) will be administered; once the 8-week supervised intervention is completed, patients will be given a recommendation to drink home-made protein shakes after non-supervised exercise. Diet supplements (protein 20 g + 300 kcal) will be prescribed to patients with severe malnutrition (twice daily), moderate malnourished (daily), or overweight (lyophilized protein 20 g once a day) for 8 weeks (induction) and then alternate days (maintenance).

#### Psychological Advice

Patients will attend an on-site or telematic visit of 1 hour led by a clinical psychologist. During this session, patients shall be given the chance to express their fears and expectations about the KT, impact of HD on health-related quality of life, compliance difficulties with medical treatments, and recommended lifestyle behaviors. After completing the physical training component, patients will be invited to participate in the standardized Mindfulness-Based Cognitive Therapy group program (MBCT), led by an expert psychologist. The MBCT program consists of 8 weekly 2-h sessions. Patients will be offered psychological counseling or treatment as needed until KT.

### Standard Medical Care

In addition to the standard medical treatment, patients will be encouraged to follow the World Health Organization global recommendations on physical activity for health in the context of daily, family, and community activities: leisure time physical activity, transportation, occupational (if still working), household chores, games, sports, or planned exercise.

### Criteria for Discontinuing or Modifying Interventions

Serious adverse events (exercise-induced arrhythmias, cardiac arrest, death) as a result of the multimodal intervention are extremely rare, but should this occur, patients will stop the intervention and continue in the “intention to treat” analysis for the primary end-point. Criteria for discontinuing the intervention include concurrent diseases or changes in the therapeutic plan. A reduced exercise tolerance will justify modification of intensity and/or progression of the protocol.

### Strategies to Improve Adherence to the Intervention Protocol

Planned strategies will include comprehensive information on the benefits of exercise, provided by the health professionals in charge of the patient's care; flexibility of the range of times to take the sessions as a way to combine trial participation and HD sessions; a choice between on-site or telematic supervision; and monthly telematic visits conducted by the physical therapist until KT. Once the intervention is completed, patients will be offered the possibility to attend optional reminder training sessions each month. Intervention adherence will be calculated for each participant. Concomitant exercise interventions are not prohibited during the trial, but the patient shall inform to the research team if this occurs.

### Relevant Concomitant Care and Interventions Permitted or Prohibited During the Trial

Any concomitant care, exercise and nutritional interventions are not permitted during the trial.

### Study Outcomes

All study outcomes are summarized in Figure 1. The **primary endpoint** will be a bad-outcome composite variable assessed at day 90 post-KT, comprising delayed graft function >14 days, never functioning kidney, non-elective readmission before day 90, surgical complications (wound healing problems, obstructive lymphocele, vascular thrombosis, urinary stenosis or leak, acute hemorrhage, immediate re-intervention), discharge to an assisted facility, or all-cause death.

**Figure 1 F1:**
[figure not shown]
Study settings and schedule of enrolment, interventions, and assessments. (a) Settings: (1) Nephrology Department; (2) Physical Medicine & Rehabilitation Department; (3) Internal Medicine Department; (4) Endocrinology Department; (5) Psychiatric Department. (b) Time of assessment will depend on starting date of the Mindfulness sessions. KT, kidney transplantation; VO2, oxygen uptake; W, workload; CPET, cardiopulmonary effort test; MLTPAQ, Minnesota Leisure-Time Physical Activity Questionnaire; BIA, bioelectrical impedance analysis; DXA, Dual X-ray Absorptiometry; PImax, maximal inspiratory pressure; PEmax, maximal expiratory pressure; SARC-F, Strength, Ambulation, Resistance, Climbing, Falls.

**Secondary outcomes** will include improvement in mid-term (6 months after intervention) and long-term outcomes (1 year after KT), as well as feasibility and safety variables. The **mid-term outcomes** will include increases in:

The proportion of non-frail patients at the end of the intervention and during pre-KT follow-up.Exercise capacity estimated by peak oxygen uptake (VO2peak) and workload (Wpeak), achieved in a cardiopulmonary effort test (CPET) expressed in mL/Kg/min and watts, respectively. A VO2peak increase of 1.5 mL/Kg/min (minimum clinically important difference) is expected to be achieved after intervention (30).Gait speed in a four-meter test.Distance traveled in a 6-min walking test (6MWT).Physical activity in the past seven days, estimated with accelerometry (total energy expenditure in Kcal, activity-related energy expenditure in MET, number of steps); total activity time will be classified as sedentary, light, moderate, and vigorous according to the Freedson Adult algorithm (31).Physical activity in the past month, assessed with a validated questionnaire.Peripheral muscle strength estimated with maximal isometric contraction of the dominant hand flexor muscles (in upper limbs) and quadriceps muscles (in lower limbs).Respiratory muscle strength estimated with inspiratory and expiratory muscle pressures (PImax and PEmax, respectively).Lean mass assessed by dual-energy X-ray absorptiometry (DXA) and bioelectrical impedance analysis (BIA).Muscle quantity and muscle quality assessed with the ultrasound parameters recommended by the Sarcopenia through Ultrasound (SARCUS) group in its 2020 update (32).Performance in activities of daily living.Performance in instrumental activities of daily living.Mindfulness dispositional traits.Patient satisfaction with multimodal prehabilitation.

Secondary **long-term outcomes** will include improvement in:

Proportion of well-nourished patients.Depression and anxiety symptoms.Personality traits.Health-related quality of life.

**Feasibility variables** will also be analyzed:

Losses to follow-up (patients not completing the follow-up assessments).Exercise tolerance (patients who adapt to intensity modification).Safety, estimated by the absence of any adverse events during the training sessions.Physical training participation (yes/no) and attendance (>80% attended sessions or home-based exercise).Mindfulness participation (yes/no) and attendance (>80% attended sessions or home-based exercise).Adherence to each of the multimodal prehabilitation components (physical activity habits, diet recommendations, and mindfulness habits).

Demographic and clinical characteristics of participants will be recorded. Anticipated variables to be used in the analysis as potential confounders include frailty assessed with the Fried phenotype (33), malnutrition, sarcopenia, comorbidity burden, personality traits, and mindfulness dispositional traits.

All patients will be assessed before and after the supervised exercise intervention, with follow-up every 6 months until KT and 1 year after KT. Time points for each outcome measurement are detailed in Figure 1.

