#### Harms

Exercise-related adverse effects (e.g., chest pain, dizziness, skeletal muscle injuries) will be recorded during the training sessions. No other unintended effects related to nutritional supplementation or psychological intervention are expected.

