## Discussion

Frailty in CKD patients displays a unique constellation of features that characterize this special population, including muscle wasting, anorexia, protein energy wasting, inflammation, oxidative stress, catabolic/anabolic hormone imbalance, metabolic acidosis, and other cellular alterations. Intervention is essential to improve quality of life for frail CKD patients, regardless of their age. Studies of post-transplant physical therapy intervention have been met with limited success, in large part due to high dropout rates. A pre-transplant clinical framework that provides multimodal prehabilitation interventions including physical therapy, nutritional measures, and psychological support may improve patient retention and compliance, better mitigate the effects of frailty and poor fitness after KT, and improve main outcomes in frail CKD patients.

Prehabilitation is more challenging in KT than in other surgical settings because the transplantation date is usually unknown. Furthermore, not all KT candidates can combine prehabilitation sessions with their HD schedules. Work schedules and geographic distance can also limit participation. In a recent survey, only 25% of HD patients were able to exercise without difficulty; the major barriers for the remaining patients were feeling too tired (55%), shortness of breath (50%), and too weak (49%) (65). If patients were to exercise, they preferred to exercise at home (73%) using a combination of aerobic and resistance training (41%), regardless of modality or age category. Finally, an extremely large sample size would be required to assess long-term outcomes like death or graft loss, as well as other important clinical outcomes that result from increased physical activity (66–68).

The main limitation is the low physical profile of many frail CKD patients, even those scheduled for KT. Consequently, some patients will not consent to undertake the intervention program and the adherence could be low, with high dropout rates. Efforts will be made by the research team to facilitate all logistical requirements and explain the strong potential benefits to the patients and their families. The process of designing the prehabilitation plan will take account of the final users' perspective in order to achieve a realistic, acceptable, user-friendly approach that covers patient needs and preferences and avoids simplistic solutions that ignore the patients' reality.

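### The safety variable is all-or-none and ignores how many sessions were done, so low attendance can make the programme look safer

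*Protocol article*

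**What the plan says.** The feasibility list in Study Outcomes defines the variable as "Safety, estimated by the absence of any adverse events during the training sessions". It gives no unit (participant or session), no analysis set and no denominator. The Harms section describes the data behind it: "Exercise-related adverse effects (e.g., chest pain, dizziness, skeletal muscle injuries) will be recorded during the training sessions".

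Exposure appears elsewhere:

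- Physical Exercise plans sessions "three times per week for 8 weeks (total 24 sessions"). Two a week are supervised, and "the third will be performed unsupervised at the patient's home".
- The same feasibility list has a separate item: "Physical training participation (yes/no) and attendance (>80% attended sessions or home-based exercise").
- The section on strategies to improve adherence adds: "Intervention adherence will be calculated for each participant".

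Statistical Methods applies intention-to-treat to the trial outcomes, adds reporting under scenarios of non-compliance and non-adherence, and names no safety set. The Discussion, after pointing to the poor physical condition of many frail patients, warns that "some patients will not consent to undertake the intervention program and the adherence could be low, with high dropout rates". The Abstract and the Introduction both name safety in the main objective, next to effectiveness and feasibility.

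**The concern.** Absence of any event is a sound summary only when everyone has about the same exposure. Here exposure may run from 0 to 24 sessions per patient. The chance of staying event-free rises as fewer sessions are done, so poor delivery of the programme and real safety push the variable in the same direction.

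The participant-level reading is likely. The neighbouring items in the list (losses to follow-up, exercise tolerance, participation) are counted per patient, and intention-to-treat is the only analysis principle stated. On that reading a patient who attends no session has no event during sessions and counts as event-free. Restricting the count to patients who started solves only part of this: someone who stops after two uneventful sessions still scores the same as someone who completes 24.

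At stake is the interpretation of a stated main objective. The article itself expects that adherence may be low and connects this with frail patients' physical condition, so the variable could be most flattering where safety is of most interest.

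**Working it through.** **Inputs from the protocol article**

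- Planned sessions: 3 per week × 8 weeks = 24, which agrees with the stated total (Physical Exercise).
- Intervention-arm sizes after the 20% allowance for losses: 23 frail and 46 non-frail (Sample Size).

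**Assumptions**

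The article gives no adverse event rate and no attendance figure. The following are therefore assumed:

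- a constant risk p per session, with independent sessions;
- non-frail patients at risk p over 24 sessions;
- frail patients at risk 2p over k sessions.

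**Step 1: effect of exposure alone**

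P(at least one event) = 1 − (1 − p)^k. At p = 1%:

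- k = 24: 1 − 0.99^24 = 21.4%
- k = 12: 1 − 0.99^12 = 11.4%
- k = 0: 0%

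**Step 2: non-attenders counted as event-free**

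Event-free share = (1 − f) × 0.7857 + f, where f is the fraction who attend nothing and the rest complete 24 sessions at p = 1%:

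- f = 0: 78.6%
- f = 10%: 80.7%
- f = 25%: 83.9%
- f = 50%: 89.3%

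Among those who started, the figure stays at 78.6% throughout.

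**Step 3: a doubled risk in frail patients**

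| p | Non-frail, 24 sessions | Frail 2p, 24 | Frail 2p, 19 | Frail 2p, 12 | Frail 2p, 8 |
|---|---|---|---|---|---|
| 0.5% | 11.3% | 21.4% | 17.4% | 11.4% | 7.7% |
| 1% | 21.4% | 38.4% | 31.9% | 21.5% | 14.9% |
| 2% | 38.4% | 62.5% | 54.0% | 38.7% | 27.9% |

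With equal attendance the doubling is plain. At 19 of 24 sessions it is attenuated. At 12 it disappears, and at 8 the order reverses.

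**Step 4: the same data per attended session**

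At p = 1% with half attendance in frail patients, and all 46 and 23 patients starting:

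- Non-frail: 46 × 24 = 1104 sessions; 1104 × 0.01 = 11.04 expected events; rate 1.0%.
- Frail: 23 × 12 = 276 sessions; 276 × 0.02 = 5.52 expected events; rate 2.0%.
- Rate ratio: 2.0.

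The contrast that the participant-level measure shows as 21.5% against 21.4% is recovered as an estimate.

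**Step 5: precision of the per-session comparison**

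SE of the log rate ratio = √(1/11.04 + 1/5.52) = 0.521. Then ln 2 / 0.521 = 1.33, and the power at two-sided 5% is Φ(1.33 − 1.96) ≈ 26%. The same calculation gives about 15% at p = 0.5% and 47% at p = 2%. The rate corrects the estimate but does not supply a conclusive test.

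**The case against.** The strongest reply is that the article fixes neither the unit nor the analysis set. Tying safety to the training sessions is compatible with counting only people who had sessions, or with reporting per session, and such details are commonly settled in an analysis plan that is not shown. This stands to the extent that scoring non-attenders as event-free is an inference. It does not remove the point: the article does state how safety is to be estimated, and the stated measure is all-or-none with no exposure term.

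Second, participation, attendance and adherence are reported alongside, so a non-attender is visible. A reader might infer that a safe programme could not be told apart from one that was not carried out. The documents do not support that, since the variables can be read together. But a separate attendance figure shows the exposure problem without adjusting the safety figure for it.

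Third, a reader might infer that a doubled risk in frail patients will be hidden. That needs about half attendance in frail patients against full attendance in non-frail patients. Both the doubling and the halving are assumptions, and they cancel almost by construction (2p × k/2 = pk). The Discussion gives no attendance figure by stratum, and part of its warning concerns people who decline to consent, who would never enter the count. Nor is a frail against non-frail safety comparison set as an objective: the specific objective on safety refers to transplant candidates as a whole.

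Fourth, it would go too far to say that the plan treats dizziness and cardiac arrest alike. The section on discontinuing or modifying interventions names serious events separately, and nothing says that events will be reported only as one binary variable.

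**Conclusion.** The point holds as an improvement to a secondary safety variable, not as an outright error. The stated measure does not relate events to sessions done. On the natural participant-level reading, low attendance makes the programme look safer: at an assumed 1% per session, halving attendance takes the proportion with an event from 21.4% to 11.4%. How far this would blur a difference between strata depends on attendance that the article does not give: nothing is lost at equal attendance, the contrast is attenuated at 19 of 24 sessions, and a doubling is hidden only near half attendance. These figures rest on constant, independent per-session risks chosen for illustration. No test or threshold is attached to the variable, and the primary endpoint is unaffected.

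**What to change.** Restate the safety variable in the feasibility list as two measures:

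- **(a)** adverse events per attended session with exact 95% limits, overall and descriptively by frailty stratum;
- **(b)** the proportion of participants with at least one event among those who started at least one session.

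Tabulate the serious events named under Criteria for Discontinuing or Modifying Interventions separately from minor ones. Keep the session count behind the >80% attendance rule as the denominator, because the dichotomy alone is not enough.

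The cost is the wording of one outcome and a small amount of extra analysis. The rule and the planned per-participant adherence calculation imply that sessions are counted, but the article does not say that the count is kept, so this should be confirmed. With about 23 frail intervention patients the intervals will be wide and power for a rate ratio of 2 is about 26% at a 1% base risk, so the strata should be described and not tested. A further split by supervised and unsupervised setting should be left out or labelled exploratory.
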